### Safety outcome

The Clinical Events Committee (CEC) reviews all adverse events to determine their severity and seriousness (SAE) and to adjudicate causality related to the procedure or the device. The latter is assessed using the following scale: “possible” (the relationship with the use of the investigational device or the relationship with procedures, is weak but cannot be ruled out completely), “probable” (the relationship with the use of the investigational device or the relationship with procedures, seems relevant and/or the event cannot be reasonably explained by another cause), and “causal relationship” (the serious adverse event is associated with the investigational device or with procedures beyond reasonable doubt).

### Primary outcomes

#### The primary efficacy endpoint

The primary efficacy endpoint is the achievement of a successful neurothrombectomy, defined as a revascularization of grade ≥2b-3 with ≤3 passes on the eTICI scale (12). The Core Lab used the eTICI scale to assess the performance of the overall system.

#### The primary safety endpoint

For the primary safety endpoint, all serious adverse events (SAEs) within 24 h (−8/+12 h) and mortality at 90 days were considered.

### Secondary outcomes

The secondary efficacy endpoint variable includes (I) good functional outcome (mRS 0–2 at 90 days post-treatment); (II) rapid neurological improvement [National Institutes of Health Stroke Scale (NIHSS) reduction >4 points or NIHSS ≤4 within 24 h]; (III) improvement at 72 h (NIHSS reduction ≥8 points or NIHSS 0–1 at 72 h or at discharge); (IV) procedure duration (time from a puncture to achieving eTICI grade ≥2b in fewer than 3 passes or final angiogram); (V) the number of passes required for recanalization; percentage of effective recanalization on the first pass; and (VI) navigability (i.e., the microcatheter and the distal access balloon catheter to reach the occlusion in the main vessel to allow navigation and deployment of the stent retriever to carry out the neurothrombectomy), assessed on a scale as “good”, “standard”, and “deficient”.

Secondary safety endpoint variable includes (I) intracerebral hemorrhage (ICH) assessed by magnetic resonance imaging (MRI)/computed tomography (CT) at 24 h, with symptomatic intracerebral hemorrhage (sICH) defined as ICH causing clinical deterioration (NIHSS worsening by ≥4 points) or death; (II) neurological deterioration (≥4 point increase on the NIHSS scale at 24 h); (III) distal embolization, i.e., any anterograde occlusion in the distal to the target artery injury, in the target ischemic territory; (IV) occurrence of embolization in previously unaffected areas on cerebral angiography; (V) mortality rate (death related to the procedure within 3 days or at discharge); (VI) procedure complications (arterial perforation and dissection—specifically involving the internal carotid artery (ICA), vasospasm, and embolization in new vascular territories); and (VII) infarction rate in previously unaffected areas (evaluated by MRI/CT 24 h post-procedure).

### Follow-up procedure

Study evaluations will be conducted at three time points: 24 h, 3 days (or at discharge), and 90 days following MT.

At 24 h post-MT (−8/+12 h), the following assessments will be performed, and relevant data will be collected: NIHSS, control neuroimaging (CT or MRI), recording of any adverse events (AEs) or SAEs, and documentation of concomitant medications.

At 3 days post-MT (±24 h) or at discharge, whichever occurs first, the following assessments will be performed: NIHSS, recording of any relevant AEs or SAEs, and determination of stroke etiology.

At 90 days post-MT, assessments will preferably be conducted through a face-to-face visit, although a telephone visit is also acceptable. Data collected will include the mRS and any SAEs resulting in death.

### Sample size determination

We anticipated that 82% of patients would achieve eTICI ≥ 2b, compared to 71.1% reported in previous research, to estimate the sample size in a non-inferiority study (13). To ensure 98% statistical power in a *Z*-test with a one-sided significance level of 0.025 and a non-inferiority margin of −2.6%, an interim analysis with 115 patients is needed (providing 51.1% cumulative information), assuming a 15% withdrawal rate. However, the sample size was increased to *N* = 225 to gather additional real-world clinical data.

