**Sample size estimates:**

The study was designed with a sequential structure based on the efficacy endpoint (eTICI ≥2b) reported in the literature [71.1% with a 95% confidence interval of (68.5%, 73.8%)]. An interim analysis was set for 115 patients and a final analysis for 225 patients, ensuring 98% power at a one-sided 0.025 significance level, with a 2.6% non-inferiority margin and a 15% assumed withdrawal rate.

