### Trial status

The analysis after 115 patients showed non-inferiority of the SEMTiC strategy using iVascular devices in achieving the primary efficacy endpoint (80% in ITT and 89% in PP populations). These 115 patients had enough statistical power to finish recruitment at that point. However, the increase in the sample size to *N* = 225 was designed to obtain additional real-life clinical data. The study completed recruitment on June 30, 2024.

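### The stated 98% power is not reached with 115 patients (about 82–94% on the stated inputs); it belongs to the planned final sample of 225

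*Protocol article*

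**What the plan says.** The Sample size determination section of the protocol article gives the inputs. On the rates: "We anticipated that 82% of patients would achieve eTICI ≥ 2b, compared to 71.1% reported in previous research". On the error rate and margin: "one-sided significance level of 0.025 and a non-inferiority margin of −2.6" percentage points. The power target is 98%, and to reach it "an interim analysis with 115 patients is needed (providing 51.1% cumulative information), assuming a 15% withdrawal rate". The next sentence begins "However, the sample size was increased to" 225 and gives additional real-world data as the reason.

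The abstract (Sample size estimates) describes the design differently: "An interim analysis was set for 115 patients and a final analysis for 225 patients, ensuring 98% power at a one-sided 0.025 significance level", with the same margin and withdrawal rate. Here the 98% belongs to a sequential design whose final analysis is at 225.

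The Trial status section follows the first account: "These 115 patients had enough statistical power to finish recruitment at that point".

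**The concern.** The article attaches one power figure to two sample sizes that differ by a factor of almost two. Both attributions cannot follow from the same rates, margin, alpha and withdrawal rate.

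This matters for how the analysis of 115 patients is read. That analysis reported non-inferiority, and the text presents it as fully powered, with the remaining patients as supplementary. If the 98% belongs to 225, the analysis at 115 was a look at about half the information, and the stated 2% risk of missing a true 82% success rate is too low for it. The reason given for 225 would also be wrong.

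**Working it through.** **Inputs.** From Sample size determination: expected rate p1 = 0.82, reference 0.711, margin 0.026, one-sided alpha 0.025 (z = 1.960), power 0.98 (z = 2.054), withdrawal 15%. From the abstract: 95% confidence interval of the reference rate 68.5% to 73.8%.

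**Derived quantities.**
- Non-inferiority limit p0 = 0.711 − 0.026 = 0.685, so the distance is d = 0.82 − 0.685 = 0.135.
- Variance at the limit: 0.685 × 0.315 = 0.2158. Variance at the expected rate: 0.82 × 0.18 = 0.1476.
- Standard error of the reference rate: (0.738 − 0.685)/(2 × 1.96) = 0.01352.
- Evaluable patients: 115 × 0.85 = 97.75, about 98; 225 × 0.85 = 191.25, about 191.

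**Step 1: where the 98% reproduces.** With the variance taken at the limit throughout, n = (1.960 + 2.054)² × 0.2158/0.135² = 190.7, so 191 evaluable. Then 191/0.85 = 224.7, so 225 enrolled. This is the stated maximum. Also 115/225 = 0.511, which is the stated 51.1% information. The 98%, the 15%, the 225 and the 51.1% all agree once the 98% is attached to 225.

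**Step 2: power at 115.** Formulas, with the full 0.025 spent at this look:
- Null variance: Φ[d√n/√0.2158 − 1.96]
- Mixed variance: Φ[(d√n − 1.96√0.2158)/√0.1476]
- Wald (variance at 0.82): Φ[d√n/√0.1476 − 1.96]
- Literature variance: Φ[d/√(0.1476/n + 0.01352²) − 1.96]
- Exact binomial against 0.685: at least 77 successes needed of 98, 89 of 115, 144 of 191

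| Form | 98 evaluable | 115 evaluable | 191 evaluable |
|---|---|---|---|
| Null variance | 82.0% | 87.6% | 98.0% |
| Exact binomial | 84.5% | 91.7% | 99.1% |
| Mixed variance | 86.6% | 91.9% | 99.4% |
| Literature variance | 90.7% | 94.1% | 99.2% |
| Wald | 93.6% | 96.5% | 99.8% |

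For example, null variance at 98: 0.135 × 9.899/0.4645 − 1.96 = 0.917, and Φ(0.917) = 0.820. Wald at 98: 0.135 × 9.899/0.3842 − 1.96 = 1.519, and Φ(1.519) = 0.936.

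**Step 3: the smallest sample for 98%.** The Wald form is the most favourable: (1.960 + 2.054)² × 0.1476/0.135² = 130.5, so 131 evaluable, and 131/0.85 = 154.1, so 155 enrolled. That is 35% above 115 (155/115 = 1.35).

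**Step 4: risk of missing a true 82% rate.** At 98 evaluable it is 6.4% (1 − 0.936) to 18.0% (1 − 0.820), about 3 to 9 times the stated 2%.

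**Step 5: what would give about 98% at 115.** Two changes do so, and neither is in the article. One-sided alpha 0.05 with all 115 evaluable gives 98.3% (Wald). Subtracting the margin a second time, from the lower confidence limit (0.685 − 0.026 = 0.659), gives 98.1% with all 115 evaluable (mixed variance).

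**The case against.** The strongest defence concerns the denominator. The endpoint is angiographic, judged within three passes, and the intention-to-treat population is everyone treated with at least one study device. Later withdrawal need not remove a patient, so 115 rather than 98 might be evaluable. With the Wald form, power is then 96.5%, only 1.5 points short. This stands as the best case, but it sets aside the withdrawal rate that the same sentence assumes, spends the whole alpha at the interim, and still falls below 98%.

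It is also fair that the article does not fix the variance form. The statistical analysis section names a Z statistic for comparing two proportions, so no single replacement figure can be imposed. Hence a range is given here, and the sponsor should name the formula.

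Low power at an interim look is normal in a sequential design. The article states no interim boundary, and the full protocol or analysis plan may do so. No figure here depends on an assumed boundary. Any boundary stricter than 0.025 would lower the interim power further.

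A reader might go further and infer that the trial is underpowered, or that the non-inferiority result at 115 is invalid. The documents support neither. On the stated inputs, 191 evaluable patients give at least 98%. Overstated power at an interim does not by itself raise the false-positive rate or bias the estimate. Nor does the word increased show that 225 was chosen after the interim data were seen: the 51.1% figure already takes 225 as full information. Finally, the Trial status sentence says enough power, not 98%, and 82–94% could be called enough by common standards. It therefore needs qualifying, not necessarily deleting.

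**Conclusion.** Wrong as written. On the article's own inputs, 115 enrolled patients give about 82–94% power with 15% withdrawal and about 88–96.5% with none. No form of the test examined reaches 98%. The 98% is the power of the design with 225 enrolled and 191 evaluable, which agrees with the abstract and contradicts the account of 225 as an increase for real-world data.

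The conclusion rests on a limit of 68.5%, a true rate of 82%, and the full one-sided 0.025 being available at the interim, which favours the plan. The literature-variance figures also take the reference rate's standard error from the abstract's interval. The error lies in the description of the interim and the reason for 225, not in the adequacy of the final sample, which has 98.0% to 99.8% power at the full alpha.

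**What to change.** Change the wording in two places.

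1. **Sample size determination.** Attach the 98% to the planned final analysis at 225 enrolled (191 evaluable). Describe 225 as the planned maximum, in line with the abstract. State the power at the 115-patient interim separately, naming the formula, the evaluable number and the alpha spent there: about 82–94% if the full 0.025 is used with 98 evaluable, and lower under any interim boundary.
2. **Trial status.** Remove or qualify the sentence that 115 patients had enough power, so that it no longer implies 98%.

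The abstract's sentence can stand, because it already ties the 98% to the design that ends at 225. No patients, data or procedures change. The only cost is a less favourable stated power at the interim.

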### Statistical analysis

All data will be analyzed with SPSS 27.0 Software. The mean ± standard deviation (SD) will be used if the data are normally distributed, and the median and interquartile range (IQR) will be used if the data are non-normally distributed.

The proportion of patients with eTICI ≥ 2b will be obtained, and the significance level for non-inferiority will be determined using the *Z* statistic for comparing two proportions with a non-inferiority margin of −0.026.

All values will be estimated using the 95% confidence interval (recommended Wilson's or Agresti methods). The following study populations will be defined for statistical analysis:

Intention to treat (ITT) is defined as all patients included in the study who have been treated with at least one of the study devices. The primary efficacy analysis in relation to non-inferiority will be performed on this population.Population by protocol (PP) is defined as ITT subset with no major deviations from the clinical investigational plan. The primary efficacy analysis in relation to non-inferiority will also be performed with this population.Modified population by protocol (PP) is defined as PP subset excluding patients treated with rescue therapy.

All outcomes will be evaluated across all study populations. The proportion of patients undergoing rescue therapy will also be measured. The impact of rescue therapy on both angiographic and clinical outcomes will be assessed using adjusted logistic regression models. A subgroup analysis will compare the results achieved in cases with the occlusion of the M2 vs. the M1/T carotid segments.

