**Design:**

SEMTiC-01 is a prospective, multicenter, single-arm, open-label clinical safety and efficacy investigation.

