This study aims to evaluate the efficacy and safety of this novel MT approach (SEMTiC strategy), which uniquely combines distal access, flow arrest, and flow reversal in a single procedure for acute ischemic stroke (AIS) patients. The non-inferiority of this combination will be compared to existing literature data.

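### The primary non-inferiority test is written as a two-proportion Z statistic, but the trial has one arm and its sample size comes from a one-sample test against a fixed 68.5%

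*Protocol article*

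**What the plan says.** The Design section describes the study in these words: "SEMTiC-01 is a prospective, multicenter, single-arm, open-label clinical safety and efficacy investigation". On the comparator, the Introduction says: "The non-inferiority of this combination will be compared to existing literature data". The Abstract gives the literature reference and its interval, in percent: "71.1% with a 95% confidence interval of (68.5%, 73.8".

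The Sample size determination section sets the assumed rates: "We anticipated that 82% of patients would achieve eTICI ≥ 2b, compared to 71.1% reported in previous research". The error rate and margin, the latter in percentage points, are a "one-sided significance level of 0.025 and a non-inferiority margin of −2.6". The section calls the test a Z-test without saying whether it is one-sample or two-sample. The Abstract describes a two-look plan: "An interim analysis was set for 115 patients and a final analysis for 225 patients". The operating figures that it attaches to this plan are 98% power at the same one-sided 0.025 level and margin, with 15% withdrawal.

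The Statistical analysis section then obtains the significance level from a Z "statistic for comparing two proportions with a non-inferiority margin"; the value given there is −0.026. It makes the ITT set the population for the primary analysis, with a repeat in the per-protocol set, and recommends Wilson or Agresti intervals for estimates. Trial status reports that non-inferiority was shown after 115 patients, with 80% success in the ITT set. No sample size for the literature comparator appears anywhere in the article.

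**The concern.** A two-proportion Z statistic has two variance terms, so it needs two denominators. This trial supplies one. To run the test as written, the analyst must either bring in a comparator size from outside the document or drop the second term and read the sentence as a one-sample test. The choice is left open, and the smallest number of successes that counts as non-inferior depends on it.

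There is also a question of principle. The margin of 2.6 points equals 71.1 − 68.5, the distance from the literature estimate to its lower confidence limit. The bar of 68.5% therefore already allows for imprecision in the literature rate. A comparator variance in the standard error charges for that imprecision a second time.

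At stake is whether a reader can reproduce the primary decision, and whether the test has the one-sided 2.5% error rate that the plan states.

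**Working it through.** **Inputs.** Reference 71.1% (68.5% to 73.8%), from the Abstract. Anticipated rate 82%, margin 2.6 points, one-sided 0.025, power 98% and withdrawal 15%, from the Abstract and Sample size determination. Interim result 80% of 115 in the ITT set, from Trial status. The bar is 0.711 − 0.026 = 0.685.

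**Step 1: the plan's own N.** For a one-sample Z-test with the variance taken at the bar:

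n = 0.685 × 0.315 × (1.960 + 2.054)² / (0.82 − 0.685)² = 190.7, so 191. Then 191/0.85 = 224.7, so 225.

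This is the stated figure exactly. A two-sample 1:1 calculation with the same inputs gives 313 per arm, or 369 after withdrawal, and does not reproduce it. The sizing therefore treats the reference as a fixed number.

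**Step 2: what comparator size the article implies.** If the literature interval is a simple binomial interval (an assumption), its half-width is (0.738 − 0.685)/2 = 0.0265, and

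n2 = 0.711 × 0.289 / (0.0265/1.96)² ≈ 1,124.

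Using the lower or upper half-width alone (0.026 or 0.027) gives about 1,168 or 1,083.

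**Step 3: the rule at N = 225 under each reading.** For each form, find the smallest count with Z ≥ 1.96. True size is the exact binomial probability of reaching that count when the true rate is 68.5%.

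| Form of the test | Successes needed of 225 | True one-sided size |
|---|---|---|
| One-sample, Wald variance | 167 | 3.6% |
| One-sample, score (variance at 68.5%) | 168 | 2.6% |
| Two-sample, n2 = 1,124 | 169 | 1.8% |
| Two-sample, n2 = 225 (equal) | 173 | 0.35% |
| One-sample exact binomial | 169 | 1.8% |

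With 191 evaluable patients, the score form, the two-sample form with n2 = 1,124 and the exact test all need 144. The equal-size form needs 148.

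**Step 4: the reported interim result.** The difference from the bar is 0.80 − 0.685 = 0.115.

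- Score: 0.115/√(0.685 × 0.315/115) = 2.65, one-sided p = 0.0040.
- Wald: 0.115/√(0.80 × 0.20/115) = 3.08, p = 0.0010.
- Two-sample, n2 = 1,124: 0.115/√(0.16/115 + 0.2055/1,124) = 2.90, p = 0.0019.
- Two-sample, n2 = 115: 0.115/√(0.16/115 + 0.2055/115) = 2.04, p = 0.021.

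All four are below 0.025.

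**Step 5: power at 82%, with the reference held fixed at 71.1% as in Step 3.** The equal-size rule has exact power 95.4% (148/191) and 97.9% (173/225). The exact binomial rule has 99.1% (144/191) and 99.6% (169/225).

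**The case against.** The strongest reply is that the phrase is loose wording for an observed proportion set against a reference proportion. The Introduction and Discussion both say that the comparison is with the literature, the sizing is one-sample, and an article may leave the formula to an analysis plan that is not shown. On that reading nothing was mis-planned. This is plausible, but the sentence states a test rather than leaving one open, and the test it states cannot be run from the article. It needs correcting in either case.

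The second reply is that the consequence is small. This stands. With the comparator size that the article's own interval implies, the two-sample rule needs 89/115, 144/191 and 169/225, identical to the exact test. Counting the literature uncertainty twice costs one success at 225 against the score form (169 against 168).

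Three stronger readings are tempting and are not supported:

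- A reader might infer that the sponsor made up a comparator size. The article does not; it leaves the size unstated.
- A reader might infer that the trial falls far short of 98% power. A figure of 88% at 191 (93% at 225) arises only if an equal-sized comparator is assumed and is itself treated as randomly sampled. Nothing suggests a 1:1 comparator, and the stated N argues against one. With the reference fixed, even that worst case keeps 95.4% and 97.9%.
- A reader might infer that the interim claim is unsound. At the stated one-sided 0.025 it holds under every form. The forms would disagree only against a stricter interim level. An O'Brien-Fleming-type level of about 0.0017, for example, falls among the p-values in the working, but the article states no boundary, so that level is an assumption.

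**Conclusion.** The point holds as a mismatch between the named test and the design. The article specifies a two-sample statistic for a one-sample trial, gives no second denominator, and sizes the study with a different test. The result is an unfixed decision rule: 167 to 173 successes at 225, with true size from 3.6% to 0.35%. The realistic range is narrower, 167 to 169, because the 173 rests on an equal-sized comparator that the documents do not suggest. The 169 for a two-sample test rests on reading the literature interval as a simple binomial one. No conclusion reported so far changes at one-sided 0.025. This is a correction that should be made for reproducibility and control of the stated error rate; it does not show that the trial is underpowered or its interim result wrong.

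**What to change.** Replace the sentence on the Z statistic with a one-sample exact binomial test of H0: p ≤ 0.685 in the ITT set, as the single decisive criterion, at the one-sided level allotted to the look in question. At the full 0.025 this means at least 169/225 (size 1.8%, power 99.6% at a true rate of 82%) or at least 144/191 (size 2.2%, power 99.1%).

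Report the Wilson interval as descriptive only. It must not be a second criterion, because it inverts the score test and the two disagree at 168/225: the Wilson lower limit is 68.6%, which clears the bar, while the exact tail probability is 0.0258, which does not meet 0.025.

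Recruitment is complete and an interim result is already reported, so also state which Z formula and which comparator input, if any, produced the claim in Trial status, and give the exact test beside it.

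The cost is a sentence or two. At 225 the exact rule asks for one more success than the score form and two more than the Wald form; at 191 it asks for the same number as the score form.

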### Patients inclusion

All patients were consecutively included when the interventional neurologist confirmed that they met all the inclusion criteria and would treat them with the proposed strategy (SEMTiC strategy), including the use of all three devices. In cases where successful reperfusion (defined as eTICI 2b-3) was not achieved after three passes with the iNdeep, iNedit, and iNtercept devices [all with European Conformity (CE) market], rescue therapy—defined as the use of any additional strategies or devices—was permitted.

Deferred informed consent was utilized to prevent delays in treatment initiation. Once a patient is considered eligible for the study, the patient or their representative receives the “Patient Information Sheet” and “Informed Consent Form” (ICF). Written consent will be required from the patient or a family member during the study period to authorize the use of patient data. Investigators will explain the study and deliver a copy of the signed ICF. Each consented patient will be assigned a unique identifier, composed of a site number and a sequential patient number, based on the order of inclusion at each site.

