### Completion of the study

All patients treated (with the study device or rescue therapy) were evaluated at 24, 72 h, or discharge and 90 days after the index procedure. The patient's study participation is considered complete at the 90-day visit.

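### The set labelled ITT admits only patients treated with a study device, so included patients in whom the strategy was not delivered belong to no analysis set

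*Protocol article*

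**What the plan says.** Four parts of the protocol article bear on who is analysed.

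- **Inclusion (Patients inclusion).** The article's rule reads: "All patients were consecutively included when the interventional neurologist confirmed that they met all the inclusion criteria and would treat them with the proposed strategy", with all three devices intended. This decision comes before any study device is used.
- **Analysis sets (Statistical analysis).** ITT is "all patients included in the study who have been treated with at least one of the study devices". Of this set the article says "The primary efficacy analysis in relation to non-inferiority will be performed on this population". The per-protocol set "is defined as ITT subset with no major deviations from the clinical investigational plan", and the modified per-protocol set removes rescued patients from that. The section adds: "All outcomes will be evaluated across all study populations".
- **Follow-up (Completion of the study).** The article's statement is: "All patients treated (with the study device or rescue therapy) were evaluated at 24, 72 h, or discharge and 90 days", counted from the procedure.
- **Navigability (Secondary outcomes).** One secondary efficacy endpoint is "navigability (i.e., the microcatheter and the distal access balloon catheter to reach the occlusion in the main vessel", so that the stent retriever can be deployed. The lowest of its three grades is deficient.

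Table 1 also excludes patients in whom another thrombectomy device was used first in the same procedure. Rescue, in Patients inclusion, means any further strategy or device, and is permitted when three passes with the study devices have not achieved reperfusion.

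**The concern.** Intention to treat is fixed by the decision to use the strategy, which the article places at inclusion. The ITT definition adds a condition that depends on what happened afterwards. A patient who was included, and in whom the operator then changed to another system before any study device counted as used, meets the inclusion rule but not the ITT rule. The other two sets are subsets of ITT, so neither recovers that patient.

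Not delivering the strategy is one of the ways the strategy can fail. In a single-arm study tested against a fixed literature rate, no control group loses comparable patients, so any such loss favours the device. If failed access attempts are not regarded as treatment, some of the failures that the navigability endpoint is meant to detect could be lost as well.

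**Working it through.** **1. Which set holds which patient.**

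| Patient | Included | ITT | PP and modified PP |
|---|---|---|---|
| Study device passes made, no rescue | yes | yes | possible |
| Three failed passes, then rescue | yes | yes | PP possible, modified PP no |
| Study catheter introduced, clot not reached, other system used | yes | depends on the undefined phrase | only if in ITT |
| Strategy intended, no study device introduced, other system used | yes | no | no |

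The last row is outside every set whatever the reading. The third row depends on wording that the article leaves open.

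**2. Inputs for the size.**

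- Reference rate 71.1%, margin 2.6 points, one-sided level 0.025 (Sample size determination). Bound: 71.1 − 2.6 = 68.5%.
- Interim success of 80% in ITT at 115 patients (Trial status). Assumption: this means 0.80 × 115 = 92 successes out of 115.
- Final size 225. Assumption: the same 80%, giving 180 of 225.
- Wilson's interval is one of the two methods recommended in Statistical analysis.
- The number of omitted patients, k, is not given. It is varied here, and every omitted patient is counted as a failure, which is the least favourable case.

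**3. Formula.** With x successes, n = 115 + k (or 225 + k), p = x/n and z = 1.96, the Wilson lower limit is

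[p + z²/(2n) − z·√(p(1−p)/n + z²/(4n²))] / (1 + z²/n).

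**4. The plan's own result first (k = 0).** For 92/115 the lower limit is 71.8%, above 68.5%. This reproduces the reported interim conclusion of non-inferiority.

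**5. Worked case, k = 5.** p = 92/120 = 0.7667. Numerator: 0.7667 + 0.0160 − 1.96 × √(0.001491 + 0.000067) = 0.7827 − 0.0773 = 0.7053. Denominator: 1 + 3.8415/120 = 1.0320. Lower limit: 0.7053/1.0320 = 0.683.

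| Omitted k | Rate | Share of included | Wilson lower limit |
|---|---|---|---|
| 0 | 92/115 = 80.0% | 0% | 71.8% |
| 2 | 92/117 = 78.6% | 1.7% | 70.4% |
| 4 | 92/119 = 77.3% | 3.4% | 69.0% |
| 5 | 92/120 = 76.7% | 4.2% | 68.3% (below bound) |
| 18, final | 180/243 = 74.1% | 7.4% | 68.2% (below bound) |

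At the final size, 17 omitted (180/242) still gives 68.53%, just above the bound.

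**6. Sensitivity to the test.** A one-sample Z with the observed variance gives 2.12 at k = 5 and 1.94 at k = 6, so it crosses 1.96 one patient later. The article describes a Z for two proportions. The literature interval of 68.5% to 73.8% implies about 1,124 patients, which adds 0.711 × 0.289/1124 = 0.000183 to the variance. At k = 5, Z = 0.0817/√(0.001491 + 0.000183) = 2.00; at k = 6, Z = 0.0753/√(0.001506 + 0.000183) = 1.83. The crossing point at the interim is therefore 5 or 6 patients under these methods.

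**The case against.** The best defence is that the threshold is low. One of three devices suffices, and one of the three is the access catheter itself. A patient in whom that catheter or the microcatheter was introduced without reaching the clot can fairly be regarded as treated with it. The navigability endpoint, with its lowest grade, suggests that such patients were meant to be assessed. This stands as a plausible reading, but the article does not state it.

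A reader might infer three stronger things that the document does not support.

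- *That every included patient is followed to 90 days, including those who had rescue instead of a study device.* The follow-up statement covers patients who were treated, not all who were included. Rescue is described as additional treatment after three study-device passes, and patients rescued in that way are already in ITT. A followed but unanalysed group is possible under the words but is not shown.
- *That navigability failures and access complications are in fact removed.* This holds only if failed attempts are not counted as treatment. The events committee reviews all adverse events, and a separate safety set may exist in the full plan.
- *That about 14% would have to be missing before the result is in doubt.* That figure (1 − 0.685/0.80 = 0.144) sets the point estimate against the bound. The decision rests on a test or confidence limit, which crosses much sooner.

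It is also fair to say that recruitment is complete and interim results are known, so replacing the primary set now would be post hoc. This affects the form of the remedy. It does not make the present definition intention to treat.

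**Conclusion.** The definition is at fault as written. The set carrying the primary test is a treated set under an intention-to-treat label, its entry condition is undefined, and no other set contains included patients in whom the strategy was intended but not delivered. Any bias from such patients favours the device.

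Its size is unknown and may be zero, because the article does not say how many included patients had no study device. On the assumptions that 80% means 92/115 and that all omitted patients are failures, 5 omitted patients (4.2% of 120) take the Wilson limit below 68.5% at the interim. On the same assumptions 18 (7.4% of 243) do so at the final size. These figures show how sensitive the conclusion is. They are not evidence that the reported result is wrong. The possible effect on navigability and safety depends further on failed access not counting as treatment.

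**What to change.** - State that any introduction of a study device, including a failed access attempt, counts as being treated with it.
- Report how many patients met the inclusion step but never had a study device, with the reason.
- Analyse the primary endpoint in all patients included under Patients inclusion whose procedure began (arterial puncture), counting non-delivery as failure. Present this beside the present set, renamed as-treated, and state that it was added after the interim results.
- Report access failures in the navigability and safety tables as they occurred. Do not assign the lowest navigability grade by rule.
- State how the Table 1 exclusion for use of another device first is applied, so that it does not remove patients switched after inclusion.

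The cost is mainly wording, one count and one further analysis. The reported success rate may fall slightly. Because consent is deferred and identifiers are given to consented patients, data on patients who never had a study device may be incomplete, and this should be stated. If the count is zero, the two sets coincide and the ITT label is justified.
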